#### Entomological

The primary entomological endpoint was the parous rate of *An. gambiae*
*s.l*. females in each study group, determined on extracted ovaries [27]. The secondary endpoint was the duration of the IVM mosquitocidal effect, determined by the mortality of insectary colonized *An. coluzzii* after feeding on IVM-treated individuals on days 7, 14, and 21 post treatment. *An. coluzzii* mortality was recorded over 14 days after feeding.

#### Social Sciences and Economics

The economics and social sciences endpoints included: (1) MDA participation and acceptability, and (2) MDA costs and cost-effectiveness. For participation and acceptability, quantitative and qualitative research methods were used. For the former, in each intervention village, a cross-sectional survey was conducted between MDA years 1 and 2. For qualitative methods, in-depth interviews and focus group discussions with MDA participants, MDA decliners, village leaders, MDA field staff, and others were carried out throughout all trial activities. Information on the costs of malaria episodes to households and their management and the intervention costs was collected to estimate costs and cost-effectiveness. From these, the incremental cost-effectiveness ratio of the intervention versus control was calculated as costs per malaria-related DALY averted. Moreover, policy considerations around translating and scaling up the intervention were explored.

### Statistical Considerations

The sample size was based on two primary endpoints: malaria prevalence determined by qPCR at the peak of the malaria transmission season and the vector population’s parous rate. For malaria prevalence, we assumed the mean malaria prevalence in the control arm at peak transmission would be 15%; this is a conservative assumption, as, in November 2013, the prevalence in villages in eastern Gambia varied between 21.3% and 44.3% [24]. Based on an initial prevalence of 15% and assuming 95%, 86%, and 63% of eligible individuals receive 1, 2, or 3 courses of DP+IVM each year, prevalence would decrease by >90% assuming “ideal conditions” such as the absence of population movement, perfect adherence and no cluster spillover effects (human/vector movement from control to intervention clusters). However, such factors may influence the effect size of the intervention. Therefore, we used a more conservative effect size of 50% or prevalence from 15% to 7.5%. Assuming a conservative coefficient of variation of 0.5, 16 clusters per arm, 200 individuals per cluster recruited in the yearly cross-sectional survey, would have 90% power to detect a significant difference between study arms.

For the vector parous rate, the assumption was that the parous rate of *An. gambiae s.l.* would be 85% because, in 2013, it was 90.7% and 81.1% in the North Bank and South Bank of the URR, respectively [24]. Therefore, assuming the intervention would decrease parity from 85% to 75%, and a coefficient of variation of 0.25, dissecting 50 *An. gambiae s.l* per village would have 90% power to find a significant difference between arms.

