## Methods

### Study Design

The study is a cluster randomized trial (ClinicalTrials.gov, NCT03576313) that included a total of 32 villages (16 control and 16 intervention), located at least 3 km from each other. A buffer zone of ~2 km was created around all intervention clusters in a modified fried-egg design [22]. No buffer zone was created around control villages. MDA with IVM plus DP was implemented in all intervention villages and the buffer zones; control villages received standard malaria interventions according to the Gambian National Malaria Control Program’s (NMCP) plans.

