To our knowledge, this is the first cluster randomized trial with a 3-day regimen of 300 µg/kg IVM (high-dose regimen). Strengths of the study include its design as an adequately powered cluster randomized trial, the setting in an area with high coverage of ITNs, IRS, and SMC, and where there is prompt and effective treatment with ACTs. Another major strength is the provision of safety data for the high dose IVM administered with DP. The trial is limited by its inability to determine the impact of IVM alone as this treatment is administered with DP, and there is no DP-only arm.

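### The 90% power stated for the vector parous rate does not follow from its own inputs, which give about 26%

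*Protocol article*

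**What the plan says.** The Statistical Considerations section of the protocol article rests the sample size on two primary endpoints: qPCR prevalence of malaria and the parous rate of the vector population. For parity the calculation runs from "assuming the intervention would decrease parity from 85% to 75%, and a coefficient of variation of 0.25, dissecting 50" mosquitoes to the conclusion that this number "per village would have 90% power to find a significant difference between arms".

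The parity sentence does not repeat the number of villages. The prevalence calculation just before it uses 16 clusters per arm, and the Study Design section says the trial "included a total of 32 villages (16 control and 16 intervention" villages. No significance level is given for either calculation.

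The Discussion (Principal Findings) then claims: "Strengths of the study include its design as an adequately powered cluster randomized trial".

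**The concern.** A CV of 0.25 on an 85% parous rate means a between-village standard deviation of 0.25 × 85 = 21 percentage points. That is about twice the 10-point effect the trial is meant to detect. With 16 villages per arm, so much variation between villages cannot be compatible with 90% power, however many mosquitoes are dissected in each.

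Parity is the endpoint that speaks to vector survival, which is the reason for adding ivermectin. If the stated inputs were right, a non-significant parity result would be the likely outcome even if the intervention worked exactly as assumed, and it could not be read as absence of an effect on vector survival. Readers would also be relying on a claim of adequate power that holds for only one of the two primary endpoints, and anyone reusing these inputs to plan another trial would be misled.

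**Working it through.** **Inputs.** All come from Statistical Considerations, except that 16 villages per arm is confirmed in Study Design. Two-sided alpha of 0.05 is an assumption.

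| | Prevalence | Parity |
|---|---|---|
| Control, p0 | 0.15 | 0.85 |
| Intervention, p1 | 0.075 | 0.75 |
| CV, k | 0.5 | 0.25 |
| Sampled per village, m | 200 | 50 |
| Villages per arm, c | 16 | 16 |
| Stated power | 90% | 90% |

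**Formula** (Hayes–Bennett, unmatched clusters, proportions):

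`V = [p0(1−p0) + p1(1−p1)]/m + k²(p0² + p1²)`

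`c = 1 + (1.96 + 1.2816)² × V/(p0 − p1)²`, where (1.96 + 1.2816)² = 10.507

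`power = Φ( |p0 − p1| / √(V/(c − 1)) − 1.96 )`

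**Step 1: reproduce the prevalence figure.** V = (0.1275 + 0.0694)/200 + 0.25 × (0.0225 + 0.0056) = 0.00098 + 0.00703 = 0.00802. Then c = 1 + 10.507 × 0.00802/0.005625 = 15.97, and power at 16 per arm is 90.05%. The match supports both the formula and the assumed alpha.

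**Step 2: apply it to parity.**
- Within villages: (0.1275 + 0.1875)/50 = 0.0063
- Between villages: 0.0625 × (0.7225 + 0.5625) = 0.0803
- V = 0.0866; SE = √(0.0866/15) = 0.0760
- Power = Φ(0.10/0.0760 − 1.96) = Φ(−0.64) = **26%**
- Villages per arm for 90%: 1 + 10.507 × 0.0866/0.01 = **92.0**

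**Step 3: see whether more mosquitoes help.** With 60 per village, power is 26.2%. With unlimited dissection only the between-village term remains: power is Φ(0.10/√(0.0803/15) − 1.96) = 27.6%, and 85.4 villages per arm would be needed. It therefore does not matter whether 50 is meant per survey, per month or per season.

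**Step 4: find what would deliver 90% with 16 villages per arm.**
- The CV required: k² = (15 × 0.01/10.507 − 0.0063)/1.285 = 0.0062, so k = 0.079.
- The effect required at CV 0.25: a fall to about 62%. At p1 = 0.62, V = 0.3631/50 + 0.0625 × (0.7225 + 0.3844) = 0.0764, SE = 0.0714, and power = Φ(0.23/0.0714 − 1.96) = 0.90.

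| CV on the parous rate | 0.05 | 0.079 | 0.10 | 0.15 | 0.20 | 0.25 |
|---|---|---|---|---|---|---|
| Power (16 per arm, m = 50) | 98% | 90% | 80% | 54% | 36% | 26% |

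**Step 5: try other conventions, with 0.25 still applied to the parous rate.**

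| Variant | Power |
|---|---|
| Divisor c instead of c − 1 | 27.4% |
| Non-central t | 26.0% |
| One-sided 0.05 | 37.1% |
| Matched-pair formula | 24.6% |
| Common SD in both arms | 23.8% |
| Beta-binomial simulation with t-test | about 30% |
| 8 control and 16 intervention villages | 17.6–19.3% |

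Reading 0.25 as an intracluster correlation instead gives 27.7%. None of these comes near 90%.

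**Step 6: apply the CV to the nulliparous fraction (15% to 25%).** V = 0.0063 + 0.0625 × (0.0225 + 0.0625) = 0.0116. Then c = 1 + 10.507 × 0.0116/0.01 = 13.2, and power at 16 per arm is 94.9%.

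**The case against.** The strongest reply is that the CV is at fault rather than the design. A standard deviation of 21 points around 85% puts one standard deviation above the mean past 100%, which is hard to believe for a parous rate. On this view 26% comes from a doubtful input and does not show that the trial is weak. **This stands**: the calculation shows that the stated inputs and the stated power are incompatible, but it does not establish the true power.

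A more specific version puts the CV on the nulliparous fraction and uses the layout of the intensive surveys, which Entomological Evaluations describes as all intervention villages but only 8 control villages. That gives 86–89% with 50 mosquitoes per village, and 89–92% with the 60 dissections mentioned in the same section, close to 90%. **This does not clear the text.** Statistical Considerations attaches the CV to the parous rate, uses 50 mosquitoes and says nothing of 8 control villages. The routine surveys covered all villages, and with 16 per arm the same reading gives about 95%.

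The 2013 parity figures (90.7% and 81.1%) do not settle the matter. Their mean is 85.9% and they differ by 9.6 points, so the CV is 4.8/85.9 = 0.056 with the n divisor, or 6.8/85.9 = 0.079 with n − 1. Both lie far below 0.25, and the second happens to equal the value needed for 90%. But two river-bank averages are weak evidence on variation between villages.

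Finally, parts of the article call malaria prevalence the primary endpoint, and that calculation is sound. However, Outcome Measures, Statistical Considerations and the Discussion all give parity primary status as well.

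**Conclusion.** The concern holds. On the inputs as written, power for the parous rate is about 26%, not 90%: a gap of 64 percentage points on a named primary endpoint. This assumes a two-sided 5% test, 16 villages per arm, and a CV that refers to the parous rate, as the text implies. The conclusion does not depend on the number of mosquitoes, the sidedness of the test or the variant of the formula.

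The power actually available depends on the true between-village CV: about 90% at 0.079, 80% at 0.10, 54% at 0.15 and 26% at 0.25. The value 0.25 is probably misstated or defined on another scale, but the article gives no way to tell. The warning about reading a null parity result applies on the stated inputs and would ease if a smaller CV were shown to be the one intended.

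**What to change.** Correct the parity paragraph in Statistical Considerations in one of two ways:

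- State the CV actually used, whether it describes the parous or the nulliparous proportion, the number of villages per arm and the significance level, together with the power these give.
- Keep 0.25 on the parous rate and report power of about 26%, with a detectable fall of about 23 points (85% to about 62%).

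In the Discussion, limit the claim of adequate power to the prevalence endpoint unless the corrected figure supports parity too.

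The cost is wording only. No villages, dissections or analyses change, and the article says statistical analysis has not begun. The sponsor may have to report a less favourable power for parity.

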### Randomization and Blinding

The unit of randomization was the village. Randomization to the intervention or the control arm was done by computer-based randomization. To prevent imbalance for potential confounding factors, restricted randomization to balance the arms on factors such as baseline prevalence, ITN coverage, and distance from health facilities was used [22].

Considering the nature of the trial (cluster randomized), the primary endpoint (malaria prevalence), and the logistical and ethical (treating thousands of individuals with placebo) challenges, we chose not to blind participating individuals. All laboratory staff involved in processing samples and evaluations contributing to any clinical or entomological endpoints were blinded to the allocation arm.

### Study Procedures and Evaluations

#### Clinical Evaluation

Passive case detection was established at local health facilities and the village level if community health workers were present. All suspected malaria cases, such as patients with fever or history of fever in the last 24 h without any other apparent illness, were investigated with an RDT (SD BIOLINE Malaria Ag Pf Standard Diagnostics); if positive, the patient was treated with artemether-lumefantrine, the first-line treatment in The Gambia. Axillary body temperature was measured using an electronic thermometer; a blood slide and blood spots were collected for later molecular analysis. Randomly selected individuals, regardless of temperature or history of symptoms, were included in the cross-sectional surveys to collect blood samples by finger prick and administer a short questionnaire on demographic characteristics, area of residence, recent travel history, and use of malaria control interventions and recent history of clinical malaria.

A cross-sectional survey to estimate the prevalence of ectoparasites, scabies, and helminths was carried out. In each cluster, 30 children aged 4-13 years, the age group at highest risk of these infections, were selected. Bedbugs were detected by visual inspection of the child’s bed using torchlight, and headlice were detected by visual search of the scalp. Scabies was identified by a complete physical examination of the body. A stool sample was taken to identify the presence of helminths, including *Strongyloides stercoralis, Trichuris trichiura*, *Necator americanus*, *Ancylostoma duodenale*, and *Ascaris lumbricoides* using PCR.

#### Entomological Evaluations

Both intensive and routine entomological surveys were performed. Intensive surveys were carried out 7-14 days after each MDA in all the intervention villages and for a similar period in 8 control villages randomly selected at the beginning of the study. The same control villages were sampled throughout the transmission season. Collections were carried out over three consecutive nights in six randomly selected houses. Monthly human landing catches (indoor and outdoor) were carried out in three houses for two nights (6 nights/month) to determine the landing rate, parity rate, sporozoite rate, and the entomological inoculation rate, and their potential reduction by IVM. Four collectors rotated between indoor and outdoor sites every 2 hours, from 7:00 pm to 7:00 am, in four selected villages per study arm. Routine surveys were carried out monthly, after the intensive surveys, between October and December, in all intervention and control villages using CDC light traps. [28]. In each village, six trapping nights/month with six indoor CDC light traps were positioned 1 m above the ground at the foot end of the bed (1 per house and protected by ITN) to obtain estimates of vector density, parity, and sporozoite rates. Parity was determined by dissecting 60 unfed *An. gambiae s.l*. (10 per trap per village) in droplets of phosphate-buffered saline (PBS) and read with a microscope at 10× field magnification. Sporozoite rate was determined by ELISA on the head and thorax of *An. gambiae s.l.*

#### Social Sciences Evaluations

A mixed-methods social science study was carried out prior to and throughout the trial. This study used ethnographic, qualitative, and quantitative methods to assess MDA coverage, potential bottlenecks to implementation, adherence, and acceptability among potential MDA participants. Before the initial MDA campaign, potential bottlenecks for the intervention were assessed, and recommendations were made to improve implementation in the first phase. These data helped fine-tune the intervention to local realities and engaged stakeholders to assure participation and long-term sustainability. In the second phase, exploratory research was conducted in all intervention and control villages to assess the MDA’s socio-cultural effects. Methods included observations of all trial components, in-depth and key-informant interviews, and focus group discussions. These methods were carried out in both the first and second years of the MDA. A quantitative household survey was conducted between years to assess findings from the first intervention year in more detail; these findings were then explored by additional qualitative and ethnographic work, including surveys, interviews, and focus group discussions in the second year.

#### Laboratory Evaluations

A finger prick blood sample was collected from all selected individuals; 40-50 µL (3 droplets) were blotted onto Whatman 3 MM filter paper and stored with a desiccant at 4°C. For the molecular detection of *P. falciparum* parasitemia, three 6-mm punches of dried blood spot, each representing approximately 8 μL blood, were added to a 96-deep well plate and used for DNA extraction. Extracted DNA was analyzed with varATS qPCR using 5 μL of extracted DNA per assay [24]. All qPCR output was analyzed using the BioRad CFX Manager software. Each plate contains two rows of *P. falciparum* standard dilution, used to make the quantification curve and allow quality control. For the serological analysis, serum was eluted from one 6-mm punch (~4 µL serum) from the filter paper. This punch was eluted in 200 µL PBS/azide to have one 1:50 predilution from which 10 µL were used on the Luminex plate. As controls for the immunoassay, BSA-coupled beads, a pool of negative sera (malaria naïve European sera), and positive sera (highly exposed Gambian sera from previous surveys) were added to each plate. Plates were analyzed and read using the MAGPIX [32]. Results were presented as the median fluorescence intensity.

### Data Capture, Management, and Analysis

Data for each participant were captured on electronic case report forms. Informed consent, demography, medical history, physical examination, vital signs, drug administration, adherence to study drugs, adverse events including serious adverse events, and laboratory evaluations were recorded.

All trial data were stored and managed within the REDCap trial database system, an application specifically designed to collect and store clinical trial data and customized for electronic data capture at the trial site. Analytical results for samples from the prevalence surveys were linked to the main trial database. When inconsistencies were found, these were checked against the original forms and subsequently amended in the dataset. All staff involved in the trial was trained on their specific tasks.

### Statistical Analysis

The primary clinical endpoint, malaria prevalence at the end of the second transmission season, will be compared between arms using random**-**effects logistic regression, and a random effect for study village will be included to account for clustering. An odds ratio, 95% CI, and *P* value will be presented. Malaria prevalence at the end of the first transmission season will be analyzed separately and in the same way.

The primary entomological endpoint, vector parity, will be compared between arms using random-effects logistic regression, and a random effect for study village will be included to account for clustering. A fixed effect for study month and year will be included. An odds ratio, 95% CI, and *P* value will be presented. Incidence will be compared between arms using random-effects Poisson regression, and a random effect for study village will be included to account for clustering. An offset for village population and a fixed effect for the study year will be included. A rate ratio, 95% CI, and *P* value will be presented. Mosquito mortality, a secondary entomological endpoint, will be determined by Kaplan-Meier estimates. Kaplan-Meier plots of mosquito survival will be presented for each age group and timepoint. A comparison between the arms will be made using survival analysis with an exponential survival model. A random effect (shared frailty) will be included for each human participant to account for correlated outcomes on mosquitoes fed on the same participant.

Other entomological endpoints: (1) Mosquito density will be compared between arms using random**-**effects negative binomial regression, and a random effect for study village will be included to account for clustering. A fixed effect for study month and year will be included. An odds ratio, 95% CI, and *P* value will be presented; (2) Sporozoite rates in field-caught mosquitoes will be compared between arms using random**-**effects logistic regression, and a random effect for study village will be included to account for clustering. A fixed effect for study month and year will be included. An odds ratio, 95% CI, and *P* value will be presented.

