### Selection of Villages and Informed Consent

A cross-sectional survey was carried out in November 2017, at the peak of malaria transmission, in 47 medium-sized (200-600 inhabitants) villages to select study villages with a baseline malaria prevalence of at least 10%. Following the survey, 32 villages with malaria prevalence determined by qPCR of at least 10% were included in the trial and randomly assigned to either the intervention or control arm using STATA, version 15; randomization was constrained such that the mean baseline prevalence in the intervention clusters was within ±10% of the prevalence in the control clusters.

After explaining the study objective and methods of the trial to the local authorities and the populations of the study villages through sensitization meetings in the local language, a census of the study population was carried out in November 2017. This was followed by individual consent procedures to obtain written informed consent for all willing residents in the study villages. Consent for children was provided by their parents/guardians; assent was sought for adolescents 12-17 years old.

Consent and enrolment procedures were carried out throughout the trial to obtain written informed consent from new residents and individuals missed previously by the research team due to absence at the time of the initial consenting and enrolment procedures.

A list of all residents in the study villages, by compound, including consent status, were generated and made available to the study team.

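### The stated primary prevalence model leaves out each village's baseline prevalence, on which the randomization was restricted, and so gives up precision if baseline predicts the endpoint

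*Protocol article*

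**What the plan says.** The protocol article, Statistical Analysis, fixes the primary comparison: "The primary clinical endpoint, malaria prevalence at the end of the second transmission season, will be compared between arms using" random-effects logistic regression, where "a random effect for study village will be included to account for clustering". The output is an odds ratio with a 95% CI and P value. No further term is listed for prevalence. The same section does list further terms for other endpoints. For parity, mosquito density and sporozoite rate it says "A fixed effect for study month and year will be included", and incidence gets a population offset and a year effect.

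The section Selection of Villages and Informed Consent reports a qPCR survey of 47 villages in November 2017. The 32 villages with prevalence of at least 10% were included, and "randomization was constrained such that the mean baseline prevalence in the intervention clusters was within ±10% of the prevalence in the control clusters". Randomization and Blinding adds that "restricted randomization to balance the arms on factors such as baseline prevalence, ITN coverage, and distance from health facilities was used".

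Statistical Considerations plans on 15% versus 7.5% prevalence, a coefficient of variation of 0.5, 16 villages per arm and 200 people per village, for 90% power. According to Results, analysis starts only after the database is locked.

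**The concern.** A village's baseline prevalence comes from the same kind of assay, in the same village and calendar month, as the endpoint. It is the natural prognostic covariate, and it exists for every village because it decided inclusion. With a coefficient of variation of 0.5, most of the variance of the arm comparison lies between villages, so a covariate that explains part of it narrows the interval without new data.

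The restriction adds a second issue. Forcing the arms to agree on baseline prevalence removes some chance imbalance from the true variability of the estimate. A model without that factor still counts the imbalance in its standard error. At stake are precision and power, not validity.

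**Working it through.** **Inputs.** From Statistical Considerations: p0 = 0.15, p1 = 0.075, m = 200, k = 0.5, c = 16 per arm. Two-sided 5% is assumed, in line with the 95% CI. The correlation r between a village's baseline and follow-up prevalence is not given, so 0.3, 0.5 and 0.7 are shown as assumptions.

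**1. The plan's own figure.** The standard unmatched cluster formula is c = 1 + (1.96 + 1.2816)² × V / (p0 − p1)², with V = p0(1−p0)/m + p1(1−p1)/m + k²(p0² + p1²).
- V = 0.000638 + 0.000347 + 0.25 × 0.028125 = 0.008016.
- c = 1 + 10.507 × 0.008016 / 0.005625 = 15.97.
- Power at 16 per arm: Φ(√(15 × 0.005625 / 0.008016) − 1.96) = Φ(1.284) = 90.05%.

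The stated 90% reproduces without adjustment.

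**2. With baseline in the model.** Replace k² by k²(1 − r²). The CI ratio is √(0.008016 / V).

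| r | V | Villages per arm for 90% | Power at 16 | Unadjusted / adjusted CI width |
|---|---|---|---|---|
| 0 | 0.008016 | 15.97 | 90.1% | 1.00 |
| 0.3 | 0.007383 | 14.79 | 92.2% | 1.04 |
| 0.5 | 0.006258 | 12.69 | 95.7% | 1.13 |
| 0.7 | 0.004570 | 9.54 | 99.0% | 1.32 |

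**3. Effect of selecting villages.** Keeping only villages at 10% or more narrows the spread of baseline and so weakens its correlation with the endpoint. Assuming lognormal village prevalence with CV 0.5 and 200 people sampled at baseline, an underlying r of 0.5 falls to about 0.36 and 0.7 to about 0.53. Step 2 then gives CI ratios of about 1.06 and 1.15, and power of about 93% and 96%.

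**4. Does the restriction make the test conservative?** Read ±10% as relative, which is ±1.5 points at 15%, and take a baseline CV of 0.5. The arm difference in baseline means has SD 7.5 × √(2/16) = 2.65 points, so the limit lies at 0.566 SD. About 43% of allocations pass, and the variance of the difference falls to about 10% of its unrestricted value. Under no effect, the between-village share of the variance is 0.01125 / 0.012525 = 0.898. The ratio of true to model variance is 1 − 0.898 × r² × 0.898, which is 0.93, 0.80 and 0.61. The nominal 5% test then has size of about 4.2%, 2.8% and 1.2%.

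That is a large-sample approximation. Simulating the random-intercept logistic model (32 villages, 200 each, 1,500 runs per scenario, relative reading, r applied without the selection in step 3) gives, for the unadjusted model:

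| r | Null rejection, Wald z | Null rejection, t with 30 df | Mean SE | Empirical SD |
|---|---|---|---|---|
| 0 | 7.1% | 6.2% | 0.216 | 0.227 |
| 0.3 | 5.7% | 4.2% | 0.217 | 0.214 |
| 0.5 | 5.1% | 4.2% | 0.218 | 0.214 |
| 0.7 | 2.3% | 1.9% | 0.218 | 0.186 |

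The small number of villages makes the Wald test liberal, and this offsets the conservatism until r is high. If ±10% means percentage points, more than 99.9% of allocations pass and Wald rejection is 6.7% to 7.6%, so the test is not conservative.

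**5. The adjusted model in the same simulation.** Mean SE is 0.206, 0.192 and 0.169 at r = 0.3, 0.5 and 0.7. Power at the planned effect, unadjusted versus adjusted (Wald z), is 93.3 vs 94.5%, 95.1 vs 96.9% and 96.4 vs 99.0%. Null rejection for the adjusted model is 6.9%, 8.1% and 7.6% with Wald z, and 5.4%, 7.3% and 7.0% with t on 30 df. Part of its apparent power gain therefore comes from a slightly liberal test.

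**The case against.** The strongest objection is scope. A journal article may leave covariates to an unseen analysis plan, and this one never calls the model unadjusted. The month and year effects listed elsewhere are design terms for repeated collections, so their presence proves little about baseline covariates. That is fair as a caution. Still, the article writes out the primary model term by term, and the change proposed is a specific improvement on that stated model.

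The second objection is size, and it largely stands. The correlation is unknown, village selection lowers it, and the endpoint comes two years after baseline. At the planned effect the simulated power gain is only about 1 to 3 points.

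Some stronger readings are tempting but unsupported:
- A reader might infer that the intervals are too wide and the test conservative as a matter of fact. That needs both a relative ±10% and a high correlation. The documents settle neither, and at r = 0.5 the simulated Wald test is close to nominal.
- A reader might infer that the parity model must include river bank, because in 2013 "it was 90.7% and 81.1% in the North Bank and South Bank of the URR, respectively", a gap of 9.6 points against a target effect of 10. The article does not say that trial villages lie on both banks or that bank was a restriction factor. Bank would shift the comparison only if the arms were imbalanced on it.
- A reader might infer that distance to a health facility belongs in the incidence model. The stated incidence analysis is not wrong without it.
- A reader might see a contradiction between the two accounts of the restriction. One gives the tolerance for a single factor and the other gives examples of factors, so they are compatible.

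**Conclusion.** The point holds as a loss of precision that is conditional on baseline prevalence predicting the endpoint. The unadjusted interval is about 4%, 13% and 32% wider than the adjusted one at assumed correlations of 0.3, 0.5 and 0.7. After allowing for village selection, the lower part of that range is more likely. Conservatism is a further possibility under a relative tolerance and a high correlation. With a percentage-point tolerance only precision is lost, and with a correlation near zero nothing is lost. The planned power is correctly calculated and is reached without adjustment, and the unadjusted analysis remains acceptable. This is a worthwhile improvement, not a correction of an error.

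**What to change.** Before database lock, define the primary model as arm, village random intercept and the logit of the village's November 2017 qPCR prevalence, plus any other factor actually used to restrict the randomization. List those factors, and state whether ±10% is relative or in percentage points. Use a small-sample t reference suited to 32 villages. Because the simulated rejection rate stayed at about 5% to 7% with t on 30 df, a permutation test over the acceptable allocations is a sensible supporting check. Keep the unadjusted model as a sensitivity analysis.

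The cost is a few lines of wording and one between-village degree of freedom per covariate out of 30: 29 remain with baseline prevalence alone, and 27 if all three named factors enter as single terms. No new data are needed.
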